#### Secondary outcomes

Secondary outcomes will include patient-reported, psychological, physical performance, and neuromuscular measures.

### Patient-reported outcome measures (PROMs)

#### KOOS

To assist the clinical interpretation of the primary outcome, we will further conduct separate analyses on all five subscales of the KOOS (Pain, Symptoms, Activities of Daily Living, Sports and Recreation, and Knee-Related Quality of Life) [49]. This granular analysis provides a comprehensive clinical basis for interpreting functional recovery across specific domains.

#### Numerical rating scale (NRS)

Pain intensity will be quantified using the NRS, ranging from 0 (no pain) to 10 (worst possible pain). We will assess the average daily pain intensity in the target knee over the preceding week, as well as the maximum intensity for resting pain (daytime and nighttime) and activity-evoked pain (during walking and stair climbing). A change of ≥ 2 points is considered clinically relevant [28].

#### Global perceived effect (GPE) scale

The GPE Scale is a simple and commonly used tool for assessing patients' subjective therapeutic efficacy, with excellent reliability [50]. Participants will rate their overall improvement by answering the prompt: 'How do you feel about your symptoms and overall condition now compared to before treatment?" [28]. Scores are based on a 7-point Likert scale, ranging from 1 (significant improvement) to 7 (significantly worse), with higher scores indicating more severe symptoms.

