### Interventions

#### The control group

Participants allocated to the Control group will continue receiving their ongoing conservative management for persistent pain after TKA, including stable medication use, self-directed physical activity or exercise, and routine medical care when necessary. No structured PNE or supervised exercise intervention will be provided during the study period.

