#### The PNE group

Participants allocated to the PNE group will additionally receive two one-hour PNE sessions delivered by a licensed physical therapist with formal training in pain neuroscience education [28]. The primary goal of PNE is to alter maladaptive pain cognitions, helping participants to reconceptualize their pain and enabling them to better self-manage their symptoms [43]. The first session (Week 0) will introduce core concepts of pain neuroscience, including peripheral and central sensitization, hyperalgesia, and the distinction between tissue damage and pain perception. Mechanisms underlying CPSP following TKA will be explained using patient-centered language and visual aids. The second session (Week 6) will reinforce previously introduced concepts, address participants’ pain-related questions, facilitate discussion of pain management experiences, and further strengthen participants' cognitive understanding and coping abilities regarding their own pain. Participants will receive a concise information booklet summarizing the PNE topics. The detailed curriculum and learning objectives for each session are outlined in Supplementary Appendix 1. Attendance at both PNE sessions is considered complete adherence to the core intervention, whereas attendance at only one session is considered partial adherence and failure to attend either session is considered non-adherence.

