#### The BFRT group

Participants in the BFRT group will additionally undergo a 12-week supervised BFRT program conducted twice weekly for a total of 24 sessions [28, 44]. Before the intervention, participants will complete three familiarization sessions separated by at least 48 h to standardize exercise technique and minimize learning effects [45]. The individualized Arterial Occlusion Pressure (AOP) will be determined using a Doppler ultrasound probe (DV-600; Marted, Brazil) in the supine position [44]. Detailed procedures for AOP measurement are provided in Supplementary Appendix 2. The training intensity will be anchored to the participant's 1-repetition maximum (1-RM) for leg press and knee extension exercises assessed using standard resistance equipment (Nakagym, São Paulo, Brazil). The 1-RM assessment protocol is detailed in Supplementary Appendix 3 [44, 46]. The intervention will follow a progressive overload model. The first week served as an adaptation phase, employing a training intensity of 20% 1-RM, completed in 4 sets of 15 repetitions each. Starting from Week 2, the training intensity was increased to 30% 1-RM, and from Week 5, the number of sets per training session was increased to 5. Inter-set rest intervals will be standardized at 1 min. During training, cuff pressure will be set at 70% of the individualized AOP, and the cuff will be inflated immediately before the first set and deflated after completion of the final set [44].

To maintain training load stability and ensure BFRT efficacy, both the 1-RM and AOP will be reassessed every 4 weeks to adjust training loads and cuff pressure based on updated values. Throughout the intervention, adverse events and participant discomfort will be continuously monitored.

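### The GPE item asks about change since 'before treatment', which has no trial-defined meaning in the Control arm, and the protocol describes the resulting change score as severity

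*Protocol article*

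**What the plan says.** The Global perceived effect section of the protocol article introduces GPE as a "commonly used tool for assessing patients' subjective therapeutic efficacy" and gives the question in full: "How do you feel about your symptoms and overall condition now compared to before treatment". No date or visit is attached to the reference point, and no separate wording is given for any arm. Answers lie on a 7-point scale "ranging from 1 (significant improvement) to 7 (significantly worse), with higher scores indicating more severe symptoms".

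On the Control arm, the protocol states: "Participants allocated to the Control group will continue receiving their ongoing conservative management for persistent pain after TKA". It adds: "No structured PNE or supervised exercise intervention will be provided during the study period". By contrast, the PNE arm "will additionally receive two one-hour PNE sessions", the first of them at Week 0, and the BFRT arm "will additionally undergo a 12-week supervised BFRT program conducted twice weekly for a total of 24 sessions". The combined arm receives both.

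Table 1 schedules GPE at Weeks 0, 12, 24, 36 and 48 in all arms. The Statistical analysis section has secondary outcomes analysed with mixed models similar to the one for KOOS₄, so GPE is compared across the four arms.

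**The concern.** A transition question is comparable between arms only if everyone looks back to the same moment. Here the moment is defined by treatment, and treatment starts within the trial in three arms but not in the fourth. Two Control participants with the same status at Week 0 and the same status at Week 12 could both answer truthfully and still differ. One compares with trial entry and reports no change. The other compares with the time before the current conservative care began and reports whatever change has occurred since then.

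If that happens more often in Control than elsewhere, part of the between-arm GPE difference reflects the period recalled rather than the intervention. Randomisation does not balance this, because it arises from what each arm is given. Assessor blinding and the mixed model cannot remove it either, because the reference point is inside the participant's answer. It also cannot be corrected after the question has been asked.

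A second, smaller problem is in the scoring sentence. The scale's end points describe change, but the sentence interprets a high score as worse symptoms. A results paper that followed it would misdescribe what GPE shows.

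**Working it through.** The protocol gives no GPE figure to reproduce, so the check compares the passages.

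**1. What 'before treatment' can refer to in each arm**

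| Arm | Treatment that starts in the trial | Treatment already under way at entry | Most natural reference point |
|---|---|---|---|
| PNE | Two sessions, Weeks 0 and 6 | Existing management, kept | About Week 0 |
| BFRT | 12-week programme | Existing management, kept | About Week 0 |
| PNE + BFRT | Both | Existing management, kept | About Week 0 |
| Control | None | Existing management, kept | Not defined by the trial |

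The third column comes from the Control group section and from the instruction, in the combined-intervention section, that all groups maintain existing medication and conservative care. It shows that the wording is loose in every arm. The arms differ in the second column: three have a treatment start inside the trial that the phrase can attach to, and Control does not.

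**2. How far back a Control participant could look.** The inclusion criteria require TKA at least 12 months earlier and pain lasting more than 6 months. The period before enrolment is therefore long, and its starting point would differ between participants. Participants are not blinded (Randomization and blinding section), so Control participants know that nothing new has begun.

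**3. Whether anything else in the article sets the anchor.** The Outcomes section, Table 1 and the Statistical analysis section give visit times and methods but do not define the GPE reference point.

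**4. Whether the effect can be sized.** Suppose a fraction p of Control participants look back to an earlier state, and this moves their answer by an average of d points. The Control mean then shifts by p × d. The protocol gives neither p nor d, nor the sign of d. If the earlier state was worse, Control looks better and active-versus-Control differences shrink. If it was better, they grow. Any figure would simply return the values assumed for p and d.

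**5. The severity wording.** Take two eligible participants, both satisfying the NRS ≥ 4 entry rule:
- A goes from NRS 9 to NRS 6, a fall of 9 − 6 = 3 points, which exceeds the 2 points that the NRS section regards as clinically relevant.
- B starts at NRS 4 and stays at NRS 4.

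On a scale that runs from improvement (1) to worsening (7), A should answer below B. If the unlabelled midpoint, (1 + 7)/2 = 4, stands for no change, B answers about 4 and A perhaps 2. B has the higher GPE score but the lower current pain (4 against 6). The scoring sentence would call B the more severe case. This step depends only on the scale's end points, not on how anyone reads 'before treatment'.

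**The case against.** The strongest reply is that the asymmetry is inferred. Control participants do have a baseline visit, and a question asked at a trial visit can reasonably be read in any arm as meaning before the trial. Active-arm participants also had TKA at least a year earlier and keep their prior care, so they too could look further back. This stands in part. A reader might infer that Control participants have no usable reference point at all, or that they will certainly answer about an earlier period. The document supports neither. It shows only that the wording leaves the reference point undefined in Control and less ambiguous elsewhere.

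A second reply is that the article is condensed and the participant-facing form or assessor script, which is not shown, may fix the anchor. That is possible. However, the article does not leave the wording to another document. It prints the prompt, and the prompt as printed carries no common anchor. If the form already contains one, the article only needs to be brought into line with it.

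A third reply is that the consequence is small. KOOS₄ is the only confirmatory outcome, and KOOS and NRS are collected at the same visits without a treatment-based reference point. This stands fully, and it limits the weight of the point. A reader might also infer that the trial stands to lose much of its power on GPE. The document gives no GPE mean, SD or power claim, so no such loss can be shown.

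Finally, the severity phrase may be called loose wording, since the end points make the direction clear and no analysis uses GPE as a severity measure. That is fair as to its weight, but the phrase is still wrong as written.

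**Conclusion.** The concern holds in a limited form. As printed, the GPE item has no trial-defined reference point for Control participants, while the three active arms have a natural one at about Week 0. The between-arm GPE comparison at Weeks 12, 24, 36 and 48 may therefore mix comparison periods in an arm-dependent way. This rests on the literal wording and on the assumption that at least some Control participants will read it that way. The direction and size of any distortion are unknown, and the document does not support calling it a proven bias for or against the interventions.

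Separately, and without that assumption, the scoring sentence misdescribes a change rating as severity.

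Both points concern one secondary outcome and leave the primary analysis untouched. They amount to a cheap improvement, worth making because answers cannot be re-anchored once given.

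**What to change.** In the Global perceived effect section, tie the item to the same event in every arm, for example: *Compared with your first study visit on [date], how are your symptoms and overall condition now?* The Randomization and blinding section has every participant complete a baseline assessment before allocation, so the common reference already exists.

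Use this wording at Weeks 12, 24, 36 and 48. A Week 0 rating would compare the first visit with itself, so the Week 0 mark for GPE in Table 1 should be removed.

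Replace the severity phrase with: *higher scores indicating less perceived improvement or more perceived worsening since study entry*.

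Recruitment is planned from May 2026. If any post-baseline GPE answers have been collected with the existing prompt, record the date of the change so that the two wordings can be told apart.

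The cost is one questionnaire line, one protocol sentence and one table entry, with no extra visits, staff or participants. The drawback is slightly less direct comparability with the cited study from which the prompt is taken.

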### Outcomes

Patients with CPSP following TKA often experience not only pain but also difficulties with activities of daily living (ADL). Since our goal is to both alleviate pain and improve physical function, we have selected the following measures as outcome indicators. Outcome assessments will be conducted at baseline, post-intervention (12 weeks), and follow-up at 24, 36, and 48 weeks [28].

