#### Pain extent and distribution

Participants will mark their habitual pain areas on a standardized anatomical body chart, and the pain pattern is classified using a knee pain map to visually assess changes in pain distribution, providing "spatial dimension" information beyond pain intensity and offering a more comprehensive reflection of pain improvement.

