### Statistical analysis

All statistical analyses will be conducted using SPSS version 27.0 (IBM Corp., Armonk, NY, USA) by statisticians blinded to group allocation. All tests will be two-tailed with a significance level set at *P* < 0.05. Baseline characteristics will be summarized using descriptive statistics. Continuous variables will be presented as mean ± standard deviation (SD) or median (interquartile range), depending on data distribution. Categorical variables will be expressed as frequencies and percentages. All efficacy analyses will follow the intention-to-treat (ITT) principle. The primary analysis will focus on evaluating whether the longitudinal response trajectory of the combined PNE + BFRT group differs from those of the comparison groups over time. To address this objective, linear mixed-effects models (LMMs) will be used for repeated-measures analyses of the primary and secondary outcomes. The primary inference of interest will be based on the group-by-time interaction effect, which reflects differential changes in outcome trajectories between intervention groups throughout the study period. To reduce the risk of type I error inflation, KOOS₄ will be considered the sole confirmatory primary outcome, while all other outcomes will be treated as secondary or exploratory. If a significant group-by-time interaction is identified for KOOS₄, post-hoc pairwise comparisons with Bonferroni correction will be performed. Secondary outcomes will be analyzed using similar mixed-effects modeling approaches. Estimated marginal mean differences with 95% confidence intervals will be reported where appropriate. Missing data will be assumed to be missing at random and handled using maximum likelihood estimation within the mixed-effects modeling framework. A supplementary per-protocol analysis, including participants with at least 80% adherence to the intervention, may also be conducted.

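### GPE is scheduled at Week 0, where its question has no answer; once that entry is removed, GPE needs a direct comparison of arms rather than group-by-time, and the classified pain pattern needs a non-linear model or description

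*Protocol article*

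**What the plan says.** All places are in the Protocol article.

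- **GPE item** (Global perceived effect (GPE) scale): participants answer "How do you feel about your symptoms and overall condition now compared to before treatment" on seven ordered points, from marked improvement (1) to marked worsening (7).
- **Schedule** (Table 1): the GPE row is marked at Week 0, in the intervention period, and at Weeks 12, 24, 36 and 48. This is the same pattern as KOOS₄, NRS, HADS and PCS. The Outcomes section agrees and makes no exception for GPE: "Outcome assessments will be conducted at baseline, post-intervention (12 weeks), and follow-up at 24, 36, and 48 weeks".
- **Order of events** (Randomization and blinding): participants are assigned only after baseline assessment is complete.
- **Pain map** (Pain extent and distribution): "the pain pattern is classified using a knee pain map to visually assess changes in pain distribution".
- **Analysis** (Statistical analysis): "linear mixed-effects models (LMMs) will be used for repeated-measures analyses of the primary and secondary outcomes". On the term to be tested: "The primary inference of interest will be based on the group-by-time interaction effect". A later sentence is looser: "Secondary outcomes will be analyzed using similar mixed-effects modeling approaches". KOOS₄ is the only confirmatory outcome.

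**The concern.** GPE is a rating of change, yet it is scheduled as if it measured a state. The description of its score points the same way: it says that higher values mean more severe symptoms, although the anchors run from better to worse. Before allocation there is no trial treatment to look back on. A Week 0 reply will be the neutral category, noise, or an answer about something else, such as the knee replacement itself.

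The analysis inherits the problem. For a state measure with a true baseline, group-by-time carries the treatment effect, because the arms start together and then separate. GPE already contains the comparison with the start, so its treatment effect is the difference between arms at follow-up. If the team later sees that Week 0 is empty and removes it, but keeps the interaction as the test, the test asks only whether the arms' differences shift between Weeks 12 and 48. A benefit that appears by Week 12 and lasts would go undetected.

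The classified pain pattern has a narrower problem. The sentence naming linear models covers it, and a linear model on nominal class codes depends on how the classes happen to be numbered.

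**Working it through.** **The plan's own figure.** The protocol gives no power figure for GPE or the pain map. Its one calculation, 128 participants for KOOS₄, reproduces as a one-way ANOVA with four groups and f = 0.34: λ = 128 × 0.34² = 14.8 on 3 and 124 df, power 0.904. It does not bear on this point.

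**Inputs.** From the protocol: 37 per arm, four arms, two-sided α = 0.05, follow-up at Weeks 12, 24, 36 and 48. Assumed, not in the protocol: GPE SD 1.2; within-person correlation ρ of 0.3, 0.5 or 0.7; a benefit constant over Weeks 12 to 48 of 0, 0.5, 0.5 and 1.0 points in Control, PNE, BFRT and the combination; no dropout. Week 0, if kept, is either near-constant (SD 0.3, uncorrelated with later ratings) or behaves like any other rating (SD 1.2, correlation ρ).

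**Formula.** Noncentrality λ = n × Σ(arm effect − mean effect)² / V, where V is the variance of the within-person quantity that carries the effect. The mean effect is 0.5, so the sum of squares is 0.25 + 0 + 0 + 0.25 = 0.5 and the numerator is 37 × 0.5 = 18.5. Power comes from the noncentral chi-square distribution.

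1. *Arm difference at Week 12* (3 df): V = 1.2² = 1.44, λ = 18.5/1.44 = 12.85, power 86.6%.
2. *Arm difference averaged over the four visits* (3 df): V = 1.44 × (1 + 3ρ)/4, which is 0.684, 0.900 and 1.116.
3. *Interaction, Week 0 kept and near-constant* (12 df): V = 0.3² + the value in step 2, which is 0.774, 0.990 and 1.206.
4. *Interaction, Week 0 kept as an ordinary rating* (12 df): V = 1.44 × (1 − ρ) × 1.25, which is 1.26, 0.90 and 0.54.
5. *Interaction, Week 0 dropped* (9 df): every difference between follow-up visits is the same in all arms (zero), so λ = 0 and power equals α, whatever the size of the benefit.

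| ρ | Arm difference, averaged | Interaction, Week 0 near-constant | Interaction, Week 0 ordinary | Interaction, Week 0 dropped |
|---|---|---|---|---|
| 0.3 | λ 27.0, 99.6% | λ 23.9, 92.9% | λ 14.7, 71.2% | λ 0, 5% |
| 0.5 | λ 20.6, 97.8% | λ 18.7, 83.6% | λ 20.6, 87.7% | λ 0, 5% |
| 0.7 | λ 16.6, 94.2% | λ 15.3, 73.6% | λ 34.3, 99.0% | λ 0, 5% |

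With Week 0 kept, the interaction has less power than the averaged arm difference in five of the six cases. It spreads the effect over 12 df instead of 3 and, when Week 0 is near-constant or only weakly correlated with later ratings, also has the smaller λ. The exception is a Week 0 rating that correlates 0.7 with later ratings and so acts as a useful covariate, which is hard to expect of a question with no referent.

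**Pain map.** No arithmetic is needed. The map has a real baseline at Week 0, so asking whether patterns change differently by arm is meaningful. Only the linear model on a nominal class is unsuitable.

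**The case against.** The strongest reply is that the plan as written keeps Week 0, and that no harm to inference then follows. Baseline assessment precedes assignment, so the Week 0 rating has the same expectation in every arm. Follow-up minus Week 0, compared between arms, then has the same expectation as the arm difference at follow-up. This is right. A reader might infer that the protocol's GPE test has only 5% power, or tests the wrong thing outright. The documents do not support that: the 5% arises only if Week 0 is removed and the interaction is kept.

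Several further points also stand.

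- A reader might infer that a GPE benefit would go unreported without a significant interaction. The stated gate on pairwise comparisons concerns KOOS₄ alone, and the section also provides for estimated marginal mean differences with confidence intervals where appropriate.
- A reader might infer that group-by-time is wrong for the pain map too. It is not, because that measure has a valid baseline.
- The looser sentence on secondary outcomes, and the description of the map as a visual aid, leave room for a categorical model or plain description in a fuller plan that is not shown.
- Preferring an ordinal to a linear model for a seven-level item is largely a modelling choice. Nothing here shows that the linear analysis of GPE would mislead.
- A constant Week 0 column might be said to distort a common-variance model, but the protocol states no covariance structure.

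What the reply cannot remove is the schedule entry. No analysis plan can make the question answerable before treatment, and correcting the entry without changing the effect term would create the blind test.

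**Conclusion.** The point holds in limited form. The Week 0 GPE mark contradicts the wording of the item and should go. While it stays, the interaction still detects a benefit (71% to 99% power), but through a baseline without meaning and usually less efficiently than comparing arms directly (94% to 99.6% averaged over visits; 87% at Week 12 alone). Once it goes, group-by-time must go with it for GPE, because power against a constant benefit is then 5%.

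The 5% needs only that the benefit is constant over Weeks 12 to 48. The other percentages rest on the assumed SD, correlations, effects and full retention; they show the ordering and are not forecasts. For the pain map, the fault is confined to the model family. All of this concerns secondary outcomes, so the point is worth acting on but does not touch the trial's confirmatory conclusion.

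**What to change.** 1. Delete the Week 0 mark in the GPE row of Table 1, and note in the Outcomes section that GPE is collected only after baseline.
2. Add a sentence to Statistical analysis: GPE is compared between arms at each follow-up visit, or averaged over Weeks 12 to 48, with estimates and 95% confidence intervals, and not through group-by-time. Choose one of the two forms in advance. An ordinal mixed model is optional.
3. Exempt the classified pain pattern from the linear-model sentence. Analyse it with a categorical mixed model, keeping group-by-time if wanted, or report it descriptively.

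The cost is one table cell and two or three sentences, and participants answer one item fewer. No change to sample size or to the KOOS₄ analysis is needed. The GPE effect should be fixed before follow-up data are seen, so that the choice does not depend on the results.
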